### fNIRS data acquisition

The fNIRS data will be acquired using the continuous wave ETG-4000 Optical Topography System (Hitachi Medical Corporation, Tokyo, Japan). This fNIRS device uses wavelengths of 695 ± 20 nm and 830 ± 20 nm as light sources and a sampling rate of 10 Hz. The optodes (10 sources and 8 detectors) will be embedded in a cap (Brain Products GmbH, Herrsching, Germany) with an inter-optode distance of 30 mm. The probesets will consist of 4 parietal channels (IPS, SMG, AG) and 5 frontal channels (MFG, IFG) per hemisphere (see Fig 1), which is a subset of channels that were previously used as a probeset [for more details on the location about the probeset see 25]. The correspondence of fNIRS channels to the underlying cortical areas was estimated based on a virtual registration method [54–56] and labeled according to the automated anatomic labeling (AAL) atlas [57].

**Fig 1 pone.0256232.g001:**
[figure not shown]
fNIRS probesets covering frontal and parietal areas of the left and right hemisphere. The probesets were fixed at P3/P4 and oriented towards F3/F4; the positions of channels and optodes (sources and detectors) including empty positions are marked [cf. 25]. *Abbreviations of the channel labels*: IFG–inferior frontal gyrus, MFG–middle frontal gyrus, SPL/IPS–superior parietal lobule/intraparietal sulcus, SMG–supramarginal gyrus, AG–angular gyrus.

### Data analysis

#### Data exclusion for subjects

Subjects will be excluded from all analysis when the inclusion criteria are not met (regarding age, handedness, language, health, and, for elderly subjects, cognition), when more than 50% of the behavioral data of the arithmetic task is missing (due to drop out or experimental or technical problems), or when the error rate in the arithmetic task is larger than 50% (because of the exclusion of incorrectly solved trials). Moreover, an outlier analysis will be conducted specific to the respective age group to exclude subjects deviating more than 3 median absolute deviations from the group’s median in RT of the arithmetic task from all analysis [58]. Subjects will be excluded only from neural data analysis in case of more than 50% missing neural data of the arithmetic task (due to drop out, experimental or technical problems, trial exclusion and artifact rejection), or in case of more than 3 noisy channels (restricting channel interpolation to a maximum of 3 channels). Furthermore, a case-wise exclusion of subjects from the respective analysis of the demographic variables (age, gender, education) or control measures (processing speed, working memory, and verbal and non-verbal intelligence) applies in case of missing or incomplete data, or an ACC below 33% in the working memory task.

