### Cognitive tests

Processing speed will be assessed by the subtest symbol search of the German version of the Wechsler Adult Intelligence Scale IV [WAIS-IV; 51]. In this paper-pencil test, subjects will be asked to decide whether or not two target symbols are present among a group of five symbols. The overall time limit is 120 s for a maximum of 60 items. The raw score (*Theoretical Range* = 0–60) is defined as the number of correctly solved items minus the number of incorrectly solved items (unsolved items are not considered). The retest reliability of the German version is good (*r*_*tt*_ = .81).

Working memory will be assessed by a verbal 2-back paradigm with letters [https://osf.io/6emdy/; 52]. The task is computerized in the program OpenSesame [50]. In this task, subjects will be asked to determine for every letter (consonants in lower and upper case) whether it matches the letter presented two positions before or not by a button press. The 92 trials consist of 30 match trials (match to the letter presented two positions before), 48 mismatch trials (no match to a letter presented one to five positions before), 6 1-back lures (match to the letter presented one position before), 6 3-back lures (match to the letter presented three positions before), and 2 start letters (presented first). Each stimulus will be presented until the button press with a time limit of 2.5 s followed by an SOA of 3 s. Accuracy (ACC) will be defined as the number of correct trials divided by the total number of trials, and RT as the duration between stimulus onset and button press. Note that the comparison between the groups will focus on ACC.

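### The 33% accuracy cut-off for the 2-back task lies below two-choice chance, and raw accuracy mixes memory with response bias in the working memory comparison

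*Protocol article*

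**What the plan says.** All references are to the protocol article.

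- **Response format (Cognitive tests).** For every letter the subject decides "whether it matches the letter presented two positions before or not by a button press".
- **Trial mix (Cognitive tests).** "The 92 trials consist of 30 match trials (match to the letter presented two positions before), 48 mismatch trials", with 6 1-back lures, 6 3-back lures and 2 start letters making up the rest. The time limit is 2.5 s per letter.
- **Score (Cognitive tests).** "Accuracy (ACC) will be defined as the number of correct trials divided by the total number of trials". The same paragraph says that the group comparison concentrates on this score.
- **Exclusion (Data exclusion for subjects).** There is "a case-wise exclusion of subjects from the respective analysis of the demographic variables (age, gender, education) or control measures" for missing or incomplete data, or for "an ACC below 33% in the working memory task".
- **Use (Statistical data analysis).** Children and the elderly are each compared with young adults on accuracy by two-sided Bayesian independent samples t-tests, ahead of the arithmetic analyses.

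The article gives no reason for 33%. It does not say how start letters or time-outs are scored, and it describes no separation of hits from false alarms.

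**The concern.** An accuracy floor in a two-choice task normally serves to remove subjects whose score carries no information on the ability measured. A floor below the guessing level cannot do that. In addition, two thirds of the trials that have a letter two positions back call for a non-match answer. An unweighted share correct therefore rewards a tendency to answer non-match, whatever the subject remembers.

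The stake is how the age groups are characterised. Under Participants, working memory is one of four control measures meant to compare general cognitive abilities. The Introduction names reduced working memory capacity as a main limit in the elderly and attributes the categorical carry and borrow effects largely to working memory load. If age groups differ in response tendency, raw accuracy could show that as a working memory difference or mask a real one.

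**Working it through.** **Inputs (Cognitive tests; Data exclusion for subjects).** 30 match, 48 mismatch, 6 + 6 lures, 2 start letters; cut-off 33%.

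**1. The plan's own figure.** 30 + 48 + 6 + 6 + 2 = 92, as stated. Non-match trials excluding start letters: 48 + 12 = 60.

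**2. Smallest score that is kept.** On 92 trials, 0.33 × 92 = 30.4, so 31 correct are needed. If start letters are left out, 0.33 × 90 = 29.7, so 30 are needed.

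**3. 50/50 guessing, all trials answered.** Expected accuracy is 50%.
- 92 trials: P(X ≤ 30) for Binomial(92, 0.5) = 0.00056, so P(kept) = 0.9994.
- 90 trials: P(X ≤ 29) for Binomial(90, 0.5) = 0.00049, so P(kept) = 0.9995.

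**4. Responding without regard to content, P(answer match) = p.** Expected accuracy is (30p + 62(1 − p))/92 if start letters count as non-matches, or (30p + 60(1 − p))/90 if they are left out. P(kept) comes from convolving the two binomials.

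| Strategy | Accuracy | P(kept) |
|---|---|---|
| Always mismatch (p = 0) | 62/92 = 67.4% or 60/90 = 66.7% | 1 |
| p = 1/3 | about 56% | about 1 |
| p = 0.8 | about 40% | 0.94 to 0.96 |
| Always match (p = 1), 92 trials | 30/92 = 32.6% | 0 |
| Always match (p = 1), 90 trials | 30/90 = 33.3% | 1 |

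If start letters stay in the denominator but a mismatch answer to them earns no credit, always mismatch gives 60/92 = 65.2%. The range is thus 65–67%. Whether a constant match responder is caught depends wholly on the unstated scoring of the start letters.

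**5. Non-response.** Suppose omissions count as errors and answered trials are guessed 50/50. With 80% of trials answered, the success probability per trial is 0.40 and P(kept) is 0.91 to 0.92. With 50% answered it is 0.25 and P(kept) is 0.04 to 0.05. Heavy non-response is therefore largely removed.

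**6. Memory against bias.** A subject with 60% hits and 70% correct rejections scores (30 × 0.60 + 60 × 0.70)/90 = 60/90 = 66.7%, the same as always mismatch. Balanced accuracy separates them: (0.60 + 0.70)/2 = 65% against (0 + 1)/2 = 50%.

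**7. Would a higher accuracy cut-off suffice?** The lowest score beating 50/50 guessing at one-sided 5% is 55/92 = 59.8% (54/90 = 60.0%). It still passes the constant mismatch responder, so the score itself has to change.

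**8. Would excluding everyone not above 50% balanced accuracy suffice?** With 30 match and 60 non-match trials, a 50/50 guesser exceeds 50% with probability 0.47. About half of pure guessers would stay.

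**The case against.** The strongest reply is that nothing confirmatory depends on this score. Working memory accuracy is not a covariate in any ANOVA or regression under Statistical data analysis. It is not among the effects of interest under Bayes factor design analysis, and the exclusion applies only to the analysis concerned. This stands and fixes the point at low priority.

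Secondly, the cut-off can be read as a floor against non-engagement and not as a test against chance. Missing or incomplete data is a separate ground for exclusion, and step 5 shows that mostly silent subjects would be removed if omissions count as errors. This stands in part. A reader might infer that the rule keeps anyone who did not do the task, and the documents do not support that. It fails for guessers and constant mismatch responders, not for heavy non-responders.

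Thirdly, a reader might infer that non-performers enter as average scorers and bias the age comparison. The article gives no expected mean or spread of accuracy for any group, no expected number of such subjects, and no evidence that response bias differs by age. No bias of a given size or direction is shown.

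Finally, removing everyone at or below chance selects on the outcome being compared. If the task is simply too hard for some children or elderly subjects, this truncates the lower tail of their group and can shrink a real difference. This stands and shapes the fix. None of these replies changes the arithmetic on the cut-off or the score.

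**Conclusion.** The point holds as a minor one. The 33% limit is below the 50% expected from guessing: a 50/50 guesser who answers all trials is kept with probability about 0.999, and always answering mismatch earns about 65–67%, roughly twice the limit. As a validity screen the rule catches little beyond heavy non-response or near-constant match answers, and the compared score cannot separate memory from response bias.

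This rests on two response alternatives and guessing that ignores content. The non-response figures also assume that time-outs count as errors. Results under the possible treatments of the start letters are shown as ranges. The effect is confined to the working memory comparison between age groups, and its size there is unknown.

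**What to change.** Before data collection, which the Proposed timeline places after in-principle acceptance:

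1. Compare groups on d-prime or on balanced accuracy, the mean of the hit rate on the 30 match trials and the correct-rejection rate on the 60 mismatch and lure trials.
2. Leave the two start letters out of the score, and state how time-outs are scored.
3. Replace the 33% rule with a non-engagement criterion, for example a high share of omitted trials or constant one-key responding.
4. Report the comparison with and without subjects whose score is not above chance, instead of dropping them outright.

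The task already elicits the match/no-match responses this needs. The cost is a slightly different score and one added sensitivity analysis.

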#### Data exclusion for trials

Trials will be excluded from the RT analysis (arithmetic and working memory task) as well as from the fNIRS analysis (arithmetic task) when the trial was not correctly solved, when the RT was below 200 ms (anticipations), when the RT deviates more than 3 median absolute deviations from the subject’s median in the respective task, and when the duration between button press and button release deviates more than 3 median absolute deviations from the subject’s median in the arithmetic task [58].

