The carry and borrow operations increase the difficulty of addition and subtraction problems as reflected by behavioral [21, 22] and neural effects [23–26]. The behavioral carry and borrow effects were already demonstrated in children [27–29], in adolescents [8, 30], in young adults [21, 22, 31], and in the elderly [32, 33]. The difficulty, as indicated by increases in reaction time and error rate, is attributed to higher working memory load, reflecting domain-general processes when comparing problems with carry and borrow operations to problems without them, i.e., the categorical carry and borrow effects [22, 34, 35]. While the categorical carry and borrow operations require place-value computation–the highest level of place-value processing–the continuous carry and borrow operations instead require place-value activation [20]. Continuous processing characteristics of the carry operation are indicated by the unit sum (e.g., 58 + 36 has a unit sum of 8 + 6 = 14), which theoretically ranges from 0 to 18 (carry operation necessary when unit sum ≥ 10); continuous processing characteristics of the borrow operation are indicated by the unit difference (e.g., 94–36 has a unit difference of 4–6 = –2), which theoretically ranges from –9 to +9 (borrow operation necessary when unit difference < 0). The carry operation is characterized by both categorical and continuous processing characteristics [31, 36]. The nature of the borrow operation, however, remains unclear, since continuous processing characteristics might not necessarily increase the difficulty of subtraction in a similar way as it is the case for addition [37].

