H1: In a task-based approach, arithmetic performance is expected to be better in young adults than in children and in the elderly. According to the developmental fronto-parietal shift for arithmetic processing, children should show increased frontal activation (left IFG and bilateral MFG) and less parietal activation (left IPS) in comparison to young adults, replicating previous research. Moreover, the neural correlates of arithmetic will be explored in the elderly: if the developmental fronto-parietal shift generalizes to the whole lifespan, the elderly might show less frontal activation (left IFG and bilateral MFG) and increased parietal activation (left IPS) in comparison to young adults; however, if arithmetic is not affected by aging or is affected and needs compensation, the elderly might show similar or increased frontal activation and similar or less parietal activation in comparison to young adults.H2: In an effect-based approach, the carry and borrow effects are expected to decrease arithmetic performance on a behavioral level (i.e., reaction times and error rates) and to be associated with larger frontal activation (left IFG and bilateral MFG) on a neural level in all age groups. Regarding the lifespan development, the behavioral carry and borrow effects are expected to be larger in children than in young adults and larger or similar in young adults as compared to the elderly, replicating previous research. The neural development of the effects will be explored here for the first time: the neural carry and borrow effects might either decrease during the lifespan, reflecting the fronto-parietal activation shift particularly for complex arithmetic, or increase during the lifespan, reflecting the more efficient use of frontal resources with increasing performance.H3: In an effect-based approach on the underlying processing characteristic, the carry and borrow effects are expected to be rather categorical in children, both categorical and continuous in young adults, and rather continuous in the elderly. On a neural level, the continuous carry and borrow effects (unit sum and unit difference) should rely on parietal activation (left IPS) in all age groups.

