### Arithmetic task

The arithmetic task will consist of two-digit addition and subtraction problems with two operands resulting in a two-digit solution [https://osf.io/6emdy/]. The carry and borrow operations will be manipulated categorically, i.e., addition problems with and without carrying (e.g., 51 + 43 vs. 58 + 36) as well as subtraction problems with and without borrowing (e.g., 94–43 vs. 94–36), and continuously, i.e., unit sum in addition (e.g., 14 in 58 + 36) and unit difference in subtraction (e.g.,– 2 in 94–36).

The stimulus set consists of 128 arithmetic problems with 32 trials per condition, i.e., addition with/without carrying and subtraction with/without borrowing. The stimulus generation will consider unit sum in addition and unit difference in subtraction to be relatively equally distributed. This means that addition problems (*a* + *b* = *r*) cannot be directly transformed by inversion into subtraction problems (*r*–*b* = *a*). Nevertheless, the numerical properties will be matched across conditions: *a* and *b* will be closely matched in their numerical magnitude and parity; the position of the larger operand will be counterbalanced; pure decades as well as ties within and between *a*, *b*, and *r* will be excluded [25, 42, for decades see 48, for ties see 49].

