The task will be computerized in the program OpenSesame [50]. Each arithmetic problem will be presented centered in white against a black background. In an oral production paradigm, the subjects will be asked to mentally solve the problem as quickly and accurately as possible and to respond while pressing the space bar. Button press and button release will be recorded and the experimenter will blindly note the given responses. Each stimulus will be presented with a time limit of 30 s and disappear upon button press to emphasize mental arithmetic before responding. In the inter-trial interval, a black screen will be shown with a duration of 4–7 s (jittered in steps of 0.5 s, mean of 5.5 s), including a white fixation point in the last 0.5 s. The 128 trials will be presented in 4 runs of 32 trials each (8 trials per condition) and the trial order will be pseudorandomized for every subject with no more than two trials of the same condition presented consecutively. As dependent variables, error rates (ER) are defined as the number of incorrectly solved and time-out trials divided by the total number of completed trials, and reaction times (RT) as the duration between stimulus onset and button press.

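### Trimming trials at 3 MAD around one median for the whole arithmetic task removes mainly slow carry and borrow trials and, if RTs are right-skewed, understates the H2 complexity effect

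*Protocol article*

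**What the plan says.** The section Data exclusion for trials begins "Trials will be excluded from the RT analysis (arithmetic and working memory task) as well as from the fNIRS analysis (arithmetic task") and then lists the grounds. One is an RT outlier rule, under which a trial goes "when the RT deviates more than 3 median absolute deviations from the" centre of that person's own responses. How that centre is defined comes next in the sentence: "median in the respective task, and when the duration between button press and button release" (the last words open the next criterion). The reference set is therefore the whole arithmetic task. The section does not say whether the MAD is raw or multiplied by 1.4826.

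The section Arithmetic task describes what is pooled: "The stimulus set consists of 128 arithmetic problems with 32 trials per condition", namely addition with and without carrying and subtraction with and without borrowing. Half of each subject's trials are thus carry or borrow trials. It also gives the upper bound of RT: "Each stimulus will be presented with a time limit of 30 s".

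The Introduction expects these conditions to differ in speed. On carry and borrow problems it says: "The difficulty, as indicated by increases in reaction time and error rate, is attributed to higher working memory load". H1 states that "arithmetic performance is expected to be better in young adults than in children and in the elderly", and H2 that "the behavioral carry and borrow effects are expected to be larger in children than in young adults".

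The section Statistical data analysis tests RT as a mean over trials in an age by operation by complexity ANOVA and mentions no transformation. The section Bayes factor design analysis names the complexity main effect and its interaction with age among the effects that drive stopping.

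**The concern.** An outlier rule should remove aberrant responses without regard to the factor under test. Here one limit per subject covers easy and hard problems together. RTs are bounded below and typically have a long upper tail, so the upper limit does nearly all the deleting. The trials above it come mostly from the slowest conditions. These are correct answers to hard problems, and their slowness is the effect that H2 measures.

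At stake are the size of the carry and borrow effects, which is a confirmatory estimate, and the comparison of that size between age groups. The same trials also leave the fNIRS models.

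**Working it through.** **The plan's own figure.** The protocol gives no figure for trimming. Its nearest figure is the 61% probability of detecting δ = 0.5 before 60 per group. A Monte Carlo run of the two-sided Bayes factor t-test (Cauchy scale 0.707, n from 20 to 60 per group, threshold 6, checked after each added subject per group) gives 61.0%. That figure reproduces and does not depend on the trimming rule.

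**Inputs from the protocol.** Four conditions of 32 trials, a 30 s limit, a 3-MAD rule over the whole task, analysis of trial means.

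**Assumed inputs.** The protocol gives no RT levels, ratios or spreads. RT is taken as 0.5 s plus a log-normal part with log-SD σ. The cell medians are b (plain addition), b·c (carry), b·s (plain subtraction) and b·s·c (borrow).

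**Hand check, assumed young-adult case** (b = 2.2 s, c = 1.4, s = 1.15, σ = 0.35)

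- Cell medians: 2.20, 3.08, 2.53 and 3.54 s.
- Untrimmed effect: b(c − 1)(1 + s)/2 · exp(σ²/2) = 2.2 × 0.4 × 1.075 × 1.063 = 1.006 s. The simulation gives 1.005.
- Simulated pooled median 2.78 s and raw MAD 0.63 s. Scaled upper limit: 2.78 + 3 × 1.4826 × 0.63 = 5.58 s. The lower limit, 2.78 − 2.80, is below zero, so the rule acts on slow trials only.
- Share above the limit: 1 − Φ(ln[(5.58 − 0.5)/(median − 0.5)]/0.35). Plain addition: z = 3.13, 0.1%. Carry: z = 1.94, 2.6%. Plain subtraction: z = 2.62, 0.4%. Borrow: z = 1.46, 7.2%. The simulation gives 0.1, 2.7, 0.4 and 7.1%.

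**Loss of complexity effect under the pooled rule, scaled MAD**

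| Assumed case (b, c, σ) | Untrimmed | Pooled rule | Loss |
|---|---|---|---|
| Young adults (2.2 s, 1.4, 0.35) | 1.005 s | 0.867 s | 14% |
| Children (5 s, 1.6, 0.50) | 3.61 s | 2.82 s | 22% |
| Elderly (2.8 s, 1.35, 0.40) | 1.14 s | 0.93 s | 18% |

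- With the raw MAD the same cases lose 28%, 37% and 33%.
- Over σ = 0.35 to 0.50 the pooled rule loses about 11-24% (scaled) or 23-39% (raw). Limits set per condition on raw RT lose about 3-5% or 6-10%.
- Over all skewed scenarios, with σ from 0.2 to 0.6, the loss runs from 3% to 33% (scaled) and from 12% to 47% (raw).
- Symmetric, equal-variance RTs: for a 0.3 s effect the scaled MAD gives 0.299 to 0.291 s, a loss of 0.008/0.299 = 2.7%, and less for larger effects. With the raw MAD the loss is 2-20%.

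**Age contrast** (between-subject variation added, scaled MAD, σ = 0.45 in children, 0.35 in young adults and 0.38 in the elderly)

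- Children minus young adults: 2.02 s untrimmed, 1.61 s pooled, 2.00 s per condition. The pooled loss is 0.41/2.02 = 20%. Standardized: d = 1.94, 1.68 and 1.84.
- Young adults minus elderly: −0.16 s untrimmed, −0.10 s pooled, −0.15 s per condition. Standardized: d = −0.25, −0.19 and −0.24.

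**Is the relative loss inherently larger in children?** With larger assumed ratios in children but the same σ in both groups, the losses in adults and children are 12% and 10% (σ = 0.30), 15% and 13% (0.35), and 23% and 19% (0.45). With σ = 0.30 in adults and 0.45 in children they are 11% and 19%. The gap comes from spread, not from the larger effect.

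**H3 slopes.** In a simulation with assumed inputs, pooled trimming flattened the unit-sum slope by 10-15% (scaled MAD). Cell-wise trimming on raw RT flattened it by 16-23%, because unit sum varies within each cell.

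**The case against.** The rule is prespecified, robust, referenced and contradicted nowhere in the document. It exists to remove lapses in an oral task with a 30 s limit, and a simulation without lapses counts every deletion as bias. With 5% lapses added, pooled trimming raised the adult within-subject standardized effect from 2.07 to 2.15 at σ = 0.30. Cell-wise MADs rest on at most 32 trials, and on fewer in error-prone cells.

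Part of this stands: trimming has a purpose, and the size of the bias rests on assumptions. It does not defend the pooling. In the same run with lapses the raw effect still fell by 12%. Cell-wise limits on log RT gave standardized effects within about 0.05 of, or above, those of the pooled rule, and lost under 1% of the effect.

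A reader might infer four stronger points that the documents do not support:

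- **Children lose relatively more because their effect is larger.** At equal log-spread they lose slightly less. The protocol gives no RT spread by age.
- **The complexity effect would be missed, or a false one created.** In the assumed cases its within-subject standardized effect stays at about 1.7 to 2.0 after trimming. With no true effect the rule creates none.
- **The fNIRS betas are shown to be biased.** The same slow trials are dropped there, so an effect is plausible, but unequal trial counts do not establish bias and none was computed.
- **Cell-wise trimming on raw RT would also repair H3.** It would still trim along the unit-sum or unit-difference slope.

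**Conclusion.** The point holds in limited form. One cut-off per subject for the whole task ties exclusion to the factor under test. Given right-skewed RTs, which are likely for timed mental arithmetic but not documented in the protocol, it biases the H2 complexity effect toward zero: by roughly 10-25% with the scaled MAD and 23-39% with the raw MAD at log-SD of about 0.30 to 0.50. The bias is negligible for symmetric RTs with the scaled MAD. Leaving the constant unstated therefore matters.

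The complexity by age contrast is also compressed in seconds, the scale analysed, if children are slower and show larger effects as H1 and H2 expect. Whether the relative loss differs by age depends on RT spread, which is unknown. The harm is to effect size and to the age contrast, more than to detection of the main effect. It does not invalidate the study, but a registered report can settle it before data collection.

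**What to change.** In Data exclusion for trials:

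1. Compute the median and MAD on log RT, within subject and within each of the four operation by complexity cells, and use these limits for both the RT and the fNIRS trial exclusions.
2. State the MAD constant (1 or 1.4826).
3. Report the RT, fNIRS and H3 regression results without RT trimming as a sensitivity analysis. H3 needs this in particular, because limits set within cells still act along the unit-sum or unit-difference slope.

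The cost is a few lines of text and code and one extra set of results, with no new data. The downside is slightly noisier MADs from at most 32 trials per cell.
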